# A multi-center randomized, controlled, open-label trial evaluating the effects of eosinophil-guided corticosteroid-sparing therapy in hospitalised patients with COPD exacerbations – The CORTICO steroid reduction in COPD (CORTICO-COP) study protocol

**DOI:** 10.1186/s12890-017-0458-7

**Published:** 2017-08-15

**Keywords:** Systemic corticosteroids, Copd, Exacerbations, Eosinophil-guided corticosteroid-sparing therapy, Randomized controlled trial, Aecopd, Gcp, Biomarker, Length of hospital stay

## Abstract

**Background:**

The most commonly applied treatment for acute exacerbations of chronic obstructive pulmonary disease (AECOPD) is a 5-day course of high-dose systemic corticosteroids. However, this treatment has not been shown to reduce mortality and can potentially have serious side effects.

Recent research has shown that, presumably, only a subgroup of COPD patients identifieable by blood eosinophil count benefit from a rescue course of prednisolone. By applying a biomarker-guided strategy, the aim of this study is to determine whether it is possible to reduce the use of systemic corticosteroids in AECOPD without influencing the outcome.

**Methods:**

This is an ongoing prospective multicenter randomized controlled open label trial comprising 320 patients with AECOPD recruited from four hospitals in Denmark. The patients are randomized 1:1 to either standard care or eosinophil-guided corticosteroid-sparing therapy where prednisolone is not administered if the daily blood sampling reveals an eosinophil level below 0.3 × 10^9^ cells/L. The primary endpoint is length of hospital stay within 14 days after recruitment. The secondary endpoints are treatment failure, 30-day mortality rate, COPD related re-admission rate, change in FEV_1_, and a number of adverse effect measures obtained within 3 months after the index hospitalisation date related to corticosteroid usage.

**Discussion:**

This will be a very large RCT providing knowledge about the effectiveness of individualized biomarker-guided corticosteroid therapy in hospitalised patients with AECOPD.

**Trial registration:**

Clinicaltrials.gov, NCT02857842, 02-august-2016. Clinicaltrialregister.eu: Classification Code: 10,010,953, 02-marts-2016.

## Background

Acute exacerbation of chronic obstructive pulmonary disease (AECOPD) often leads to hospitalization and is associated with a high mortality rate. AECOPD episodes lead to accelerated decline in lung function and have negative impact on physical activity and quality of life. Furthermore, AECOPD implies high socioeconomic costs [1]. For decades, systemic corticosteroids have been a cornerstone in management of moderate to severe AECOPD. However, the optimal approach as regards the duration of treatment is unknown [2]. The REDUCE study concluded that a 5-day course of systemic corticosteroids is noninferior to 14-days of treatment [3]. Based on this, the recent GOLD strategy document recommends five to seven days of systemic corticosteroid treatment for patients with AECOPD [4].

### Previous research

A more recent Cohrane review (13 studies contributed data, *n* = 1620) regarding AECOPD patients has shown that systemic corticosteroids (compared to placebo) reduce the risk of treatment failure (number needed to treat (NNT) = 9; 95% confidence interval (CI) 7 to 14). Treatment failure was defined as patients who within 30 days required hospitalization or emergency room visits or patients requiring add-on pharmacological maintenance therapy. The risk of recurrence of AECOPD was also reduced within the first month (hazard ratio (HR) 0.78; 95% CI 0.63 to 0.97), whereas no difference in AECOPD recurrence was observed during the following 3 months [3].

Lung function measured up to 72 h after first administration of systemic corticosteroids showed significant improvement in forced expiratory volume in 1 s (FEV_1_) in the corticosteroid group (mean difference (MD) 140 mL; 95% CI 90 to 200), whereas this difference was not observed at later time-points. No difference was observed in mortality (odds ratio (OR) 1.0; 95% CI 0.60 to1.66). The total length of hospital stay (LOS) was shorter in the corticosteroid-treated group (MD −1.22 days; 95% CI -2.3 to −0.2), whereas there was no difference in the LOS in intensive care unit. The risk of steroid induced side effects was, as expected, increased (OR 2.33; 95% CI 1.59 to 3.43) in the corticosteroid-treated group compared with the control group; number needed to harm (NNH) = 6; 95% CI 4 to 10). Meanwhile, the proportion of side effects in the corticosteroid group (48.1%) was considerably higher than the control group (28.5%). The risk of hyperglycemia was increased (OR 2.79; 95% CI 1.86 to 4.19) and the absolute risk was 28.2% [3]. Others have identified serious psychiatric side effects (depression, mood changes, psychosis) and serious somatic side effects such as hypertension, ulcers, secondary adrenal insufficiency, diabetes, osteoporosis and increased risk of bone fractures in patients exposed to long-term systemic corticosteroids [5–7].

Earlier, the inflammatory process in patients with AECOPD was believed to be homogeneous, primarily neutrophilic. However, recent studies have shown that both inflammation [8, 9] and ethiology [10–12] are heterogeneous. It has been demonstrated that a subgroup of patients with AECOPD have eosinophilic inflammation [13]. Specific attention on biological clusters and biomarkers of these have resulted in an increased understanding of the differentiated inflammatory mechanisms that exist in AECOPD [14]. Examinations of sputum from the airways in smokers have increased this understanding further [15].

A small randomized study (*n* = 109) of COPD patients with moderate exacerbations has indicated that blood eosinophil-guided corticosteroid treatment might reduce the use of systemic corticosteroids in exacerbations by 49% without simultaniously worsening of symptoms and increasing risk of treatment failure compared with standard care [16]. Furthermore, patients with initial low eosinophil count more often experienced treatment failure if they had received corticosteroid therapy rather than if they had not (15% treatment failure in prednisolone group, 2% treatment failure in corticosteroid-saving group, *p* = 0.04). However, the study had no impact on current recommendations due to the limited sample size. Larger cohort studies documented that diagnosed COPD patients with daily symptoms have more than 3-fold increased risk for AECOPD if they have an eosinophil count ≥0.34 × 10^9^ cells/L [17].

So, the question that remains to be answered based on the currently available studies is whether the clinical effects of systemic corticosteroid treatment in hospitalised patients with AECOPD can be achieved via a more targeted and individualized eosinophil-guided treatment rather than the current “one-size fits all” treatment. To our knowledge, no randomized clinical trials have yet examined this field. This study will address this important question. The aim is to determine whether it is possible to reduce the use of systemic corticosteroids in AECOPD without influencing the outcome by applying a biomarker-guided strategy. Additionally, the study will explore whether this strategy reduces some of the most frequent side effects that occur with the current standard treatment.

## Methods

### Objective

The overall objective is to determine whether a prednisolone regimen with lower accumulated doses in hospitalised patients with AECOPD have noninferior clinical outcome than when applying standard care (SC). Based on a sufficiently sized (powered) clinical study, the aim is to determine if there is no relevant increase in LOS for AECOPD patients receiving eosinophil guided prednisolone-sparing therapy compared to SC. The primary endpoint of this analysis is LOS defined as the time from hospital admission to hospital discharge within 14 days after recruitment. The secondary objective is to determine if the clinical outcome for patients receiving eosinophil guided corticosteroid-sparing therapy will not be less favourable compared to SC. The following endpoints will be included when assessing the clinical outcome: 30-day mortality rate, treatment failure, COPD related re-admission rate, changes in FEV_1_, changes in health-related quality-of-life measured by COPD Assessment Test (CAT), changes in level of dyspnoea using the modified Medical Research Council (mMRC) Dyspnoea Scale, cumulative systemic corticosteroid dose, the period between index AECOPD and the next AECOPD and a number of adverse effect measures between index hospitalization and 3 month follow-up. The adverse effect measures include hyperglycemia, osteopenia (Bone Turnover Markers: C-terminal telopeptide of type 1 collagen (CTX) and procollagen type 1 N propeptide (P1NP)), osteoporotic fractures, dyspepsia or ulcer complications (gastrointestinal bleeding), onset of diabetes mellitus (defined as HbA1c ≥ 48 mmol/mol) or worsening of diabetes mellitus (defined as initiation/intensification of anti-diabetic treatment), increase in Body Mass Index and new infections treated with antibiotics since study entry.

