### Measurements

All outcome measures will be recorded at baseline and at the one and three month follow up visits (Table 1). On the baseline visit (during hospitalization), the following variables will be noted: sociodemographic data (e.g. sex, age, height, weight, ethnicity), smoking history, pack-years, co-morbidities (including the presence of diabetes, heart failure, ischemic heart disease, atrial fibrillation, essential hypertension, hypercholesterolemia), employment status, support with activities of daily living at home, clinical symptoms (increased dyspnea, increased sputum volume, and increased sputum purulence (Anthonisen criteria), increased cough), disease symptoms duration, body mass index (kg/m^2^), number of exacerbations in the past, atopy status, mean cumulative systemic corticosteroid dose (mg) 4 weeks before study entry, use of oxygen therapy, use of noninvasive mechanical ventilation, vital signs, adverse events to systemic corticosteroids, medication adherence by day 5, arterial blood gases and Ca^2+^, blood samples, findings from Chest X-ray and spirometry will be collected and stored on Case Report Forms in pseudoanonymised format at the treatment site (Table 1). Furthermore, patients will be requested to complete the CAT and mMRC Dyspnoea Scale. Follow-up visits will be conducted one and three months after discharge. If the patient does not attend the visit, the patient will be contacted for a new follow-up or - if not able to meet for an appointment at the hospital - a home visit by a doctor assigned to the project. At the one month and the three month follow up visits the following data will be assessed: BMI, HbA1c (only at the one month follow-up), spirometry values, CAT score, mMRC, CTX, P1NP, PTH (only at the three month follow-up), D-vitamin status (only at the three month follow-up), cumulative systemic corticosteroid dose, the period between index AECOPD and the next AECOPD, COPD related re-admission rate, dyspepsia or ulcer complications (gastrointestinal bleeding) and new infections treated with antibiotics since study entry.

**Table 1 Tab1:** Data collected at baseline and follow-up visits

Data collected	Study period		
	Baseline	1-month	3-month
Demographics	X		
Daily blood glucose measurements	X		
Daily leukocyte differential count^a^	X		
Arterial blood gases and Chest X-ray	X		
Testing for diabetes (HbA1c)	X	X	
Spirometry	X (day 1 + day 3)	X	X
Height measurement & vital signs	X		
Weight measurement	X	X	X

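### The one HbA1c-based harm endpoint is a yes/no event, although HbA1c is scheduled at baseline and one month in both arms; a baseline-adjusted comparison on the full scale would use far more of the information

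*Protocol article*

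**What the plan says.** The Objective section of the protocol article lists the adverse effect measures. The diabetes item reads "onset of diabetes mellitus (defined as HbA1c ≥ 48 mmol/mol) or worsening of diabetes mellitus (defined as initiation/intensification of anti-diabetic treatment". Both parts are yes/no events: one is a laboratory value at or above a cut, the other a change in treatment.

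The same section lists FEV1, CAT and mMRC as changes and BMI as an increase. It lists no change in HbA1c.

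The Measurements section names the follow-up data as "BMI, HbA1c (only at the one month follow-up), spirometry values, CAT score, mMRC, CTX, P1NP" and further items. Table 1 has a row "Testing for diabetes (HbA1c") marked at baseline and at one month. The footnote that limits a test to the intervention group belongs to the leukocyte count, so HbA1c is scheduled in both arms.

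On the status of the harm question, the section on previous research says "the study will explore whether this strategy reduces some of the most frequent side effects that occur with the current standard treatment".

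**The concern.** HbA1c is a continuous measurement taken twice. Cutting the second value at 48 mmol/mol means that a shift counts only in patients whose value it carries across the line. A patient who moves from 38 to 41 contributes nothing.

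The randomised contrast is modest. Under Study design, randomization and intervention, both arms receive the first-day intravenous dose, and they differ by at most four tablet days. Any HbA1c shift is therefore likely to be small, which is where a cut performs worst.

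For worsening of known diabetes, the HbA1c value is not used at all. The event is a decision to start or intensify treatment, and in an open-label trial the arm can be known to those who make it. Knowledge of the arm cannot directly alter the laboratory value.

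At stake is one exploratory harm comparison. A finding of no difference in new or worsened diabetes could be read as no glycaemic benefit, when the endpoint as defined had little chance of showing one.

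**Working it through.** **The plan's own figure.** The only power statement is for length of stay (SD 3.81 days, margin 1.2 days, 80% power, two-sided 5%). Per arm, n = 2 × (1.960 + 0.842)² × 3.81² / 1.2² = 158.3, so 159 per arm and 318 in total. With the t distribution it is 160 per arm, which is the stated 320. The figure reproduces, but it says nothing about HbA1c.

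**Inputs for HbA1c.** The documents give no mean, SD, correlation, event rate or expected effect. All of these are assumptions:
- 136 per arm without diabetes at entry (85% of 160), baseline HbA1c below 48 mmol/mol
- mean 39, SD 5 mmol/mol
- correlation of 0.8 between baseline and one month, with 0.6 as an alternative
- true difference between arms of 0.3 to 1.5 mmol/mol
- two-sided 5%

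**Full scale, adjusted for baseline.** Residual SD = 5 × √(1 − 0.8²) = 3.0. Standard error of the arm difference = 3.0 × √(2/136) = 0.364. Power ≈ Φ(difference/0.364 − 1.96), plus a small opposite tail.
- Difference 1.0: Φ(2.75 − 1.96) = 78%
- Difference 0.5: Φ(1.37 − 1.96) = 28%
- Difference 0.3: Φ(0.82 − 1.96) = 13%

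**Cut at 48.** At a difference of 1.0, simulation gives about 2.4% v 4.2% crossing the line. Standard error = √(0.024 × 0.976/136 + 0.042 × 0.958/136) = 0.0216, and 0.018/0.0216 = 0.83. Power ≈ Φ(0.83 − 1.96) = 13%. Direct simulation gives 11% to 12%.

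**Simulated power, cut v ANCOVA, 136 per arm, mean 39, SD 5:**

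| True difference (mmol/mol) | Correlation 0.8 | Correlation 0.6 |
|---|---|---|
| 1.5 | about 21–24% v 98% | 23% v 87% |
| 1.0 | about 12% v 77% | 11% v 53% |
| 0.5 | about 5% v 27% | 6% v 17% |
| 0.3 | about 5% v 13% | 5% v 9% |

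At a difference of 0.3 and correlation 0.8, shorter simulation runs ranged from 4% to 5% for the cut and from 12% to 16% for ANCOVA. The longest run (20,000 repeats) and the formula both give 13% for ANCOVA.

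**Other inputs.** With 160 per arm, a difference of 1 mmol/mol, means 38 to 42, SD 4 to 5 and correlation 0.6 to 0.9, power was 8–28% for the cut and 61% to over 99% for ANCOVA. In sample-size terms the cut kept about 1% to 25% of the efficiency of the adjusted analysis.

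**Patients with known diabetes.** One run that added 15% with known diabetes (160 per arm in all) gave 11% v 60% at a difference of 1.0. That 60% corresponds to a residual SD of about 4.0 instead of 3.0: 4.04 × √(2/160) = 0.452, and Φ(1/0.452 − 1.96) = Φ(0.25) = 60%. A wider spread in these patients would lower the gain further. The treatment-change events were not modelled, because the documents give nothing to model them with.

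**The case against.** Much of the case on the other side is sound.

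- **The list is open.** It is introduced by "The adverse effect measures include hyperglycemia, osteopenia" and so on, and the Measurements section names HbA1c itself as follow-up data. An analysis plan that is not shown could add a continuous analysis. This stands, so it cannot be said that HbA1c will be used only as a yes/no variable. It does not remove the point, because the protocol has itself chosen the scale and cut of the one HbA1c endpoint that it defines.
- **Other harm measures exist.** Hyperglycaemia is listed separately, Table 1 schedules "Daily blood glucose measurements", and CTX, P1NP and BMI are also listed. A reader might infer that the trial loses most of its power to show less steroid harm. The documents do not support that: the loss concerns the HbA1c-based measure alone.
- **No power is claimed.** The protocol says only that "the study will explore whether this strategy reduces some of the most frequent side effects". No stated figure is wrong.
- **The effect may be too small.** At a difference of 0.2 to 0.3 mmol/mol the gain is only about 2 to 8 percentage points in the simulations, and both analyses are weak. A reader might infer that the full-scale analysis would rescue the endpoint. Nothing in the documents shows a shift large enough for that.
- **Onset of diabetes is a clinical diagnosis and needs a threshold.** That is a reason to keep the count, but not to leave the measured values out of the comparison.

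**Conclusion.** The point holds as an efficiency weakness in one exploratory harm measure. The only HbA1c-based endpoint that the protocol defines reduces paired continuous values to a threshold crossing or to an open-label treatment change, and that discards most of the information. ANCOVA did better than the cut in every scenario tried.

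The size is conditional. Under the central assumptions the gain is about 65 percentage points of power at a true difference of 1 mmol/mol (12% to 77%), about 22 at 0.5 (5% to 27%) and about 8 at 0.3 (5% to 13%). None of these inputs comes from the documents, and the figures cover patients without diabetes at entry. Both arms have HbA1c scheduled, but deaths and missed visits will reduce the number with a one-month value. The primary endpoint and the stated sample size are not touched.

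**What to change.** Before the data are analysed, name one-month HbA1c on its full scale as a harm endpoint. Compare the arms by ANCOVA, with baseline HbA1c and known diabetes at entry as covariates, in all randomised patients with a measurement. Report the adjusted mean difference with its 95% confidence interval. Keep onset (HbA1c at or above 48 mmol/mol) and worsening (treatment change) as clinical event counts beside it. The treatment-change count is also needed to interpret HbA1c in patients with diabetes, whose value can fall because treatment was intensified.

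The cost is one sentence and one model, with no new visits, samples or patients. The downside is small: one more exploratory comparison, and a mean difference in mmol/mol that is less directly clinical than a count of new diabetes.

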### Study design, randomization and intervention

The study will be conducted as a prospective, multicenter, randomized, controlled, open-label study in hospitalised patients with AECOPD. In total, 320 patients are expected to be included in the project within 24 months. Patients will be randomly assigned in a 1:1 fashion to either an intervention group where guidance of prednisolone treatment is based on daily eosinophil count (“eosinophil-guided corticosteroid-sparing therapy”) or a standard group in which guidance of prednisolone is based on an existing guideline, see below. Pre-stratified block randomization with blocks of varying (and blinded) size will be applied to ensure equal distribution of patients on site (four different pulmonary departments in Denmark) and age (above or below 70 years of age). The study was monitored according to Good Clinical Practice (GCP) by the GCP unit at Bispebjerg University Hospital, Copenhagen, Denmark.

Patients will be randomized to one of the two treatment arms:Standard Care (SC) group: Intravenous methylprednisolone 80 mg on the first day followed by 37.5 mg of prednisolone tablets daily for 4 days.Intervention group: Intravenous methylprednisolone 80 mg, followed by prednisolone tablet 37.5 mg daily (maximum of 4 days in all) on days where the blood eosinophil count is ≥0.3 × 10^9^ cells/L. On days with eosinophil count <0.3 × 10^9^ cells/L systemic corticosteroid treatment will not be administered.

If a patient is discharged during the treatment period, a treatment based on the last measured eosinophil count will be prescribed for the remaining days within the 5 day-period.

#### Selection of participants

All consecutive patients admitted with AECOPD in participating centres will be considered for study enrolment (Fig. 1). Fulfilling the inclusion and exclusion criteria, patients will be invited to participate in the project. The aim is to enroll a sample representative of hospitalized patients with AECOPD in Denmark. Subjects on chronic systemic corticosteroids will be eligible for inclusion if they are receiving systemic corticosteroids corresponding to 5–10 mg daily. Patients receiving non-invasive ventilation (Continuous Positive Airway Pressure/Bilevel Positive airway pressure) were only recruited if they were admitted at one of the four recruiting departments.

**Fig. 1 Fig1:**
[figure not shown]
Flowchart of patients through the study

### Inclusion criteria

Hospitalized patients with AECOPD within 24 h after admissionAge ≥ 40 yearsSpirometry-verified COPD (defined as postbronchodilator FEV_1_/FVC ≤ 0.70)

### Exclusion criteria

Self-reported physician diagnosed asthmaLife expectancy less than 30 daysSevere COPD exacerbation requiring invasive ventilation or admission to ICUAllergy to systemic corticosteroidsSevere mental illness which is not controlled by medicationPeople who are detained under the act on the use of coercion in psychiatrySevere language difficulties or inability to provide written informed consentPregnancy and lactationSystemic fungal infections

### Measurements

All outcome measures will be recorded at baseline and at the one and three month follow up visits (Table 1). On the baseline visit (during hospitalization), the following variables will be noted: sociodemographic data (e.g. sex, age, height, weight, ethnicity), smoking history, pack-years, co-morbidities (including the presence of diabetes, heart failure, ischemic heart disease, atrial fibrillation, essential hypertension, hypercholesterolemia), employment status, support with activities of daily living at home, clinical symptoms (increased dyspnea, increased sputum volume, and increased sputum purulence (Anthonisen criteria), increased cough), disease symptoms duration, body mass index (kg/m^2^), number of exacerbations in the past, atopy status, mean cumulative systemic corticosteroid dose (mg) 4 weeks before study entry, use of oxygen therapy, use of noninvasive mechanical ventilation, vital signs, adverse events to systemic corticosteroids, medication adherence by day 5, arterial blood gases and Ca^2+^, blood samples, findings from Chest X-ray and spirometry will be collected and stored on Case Report Forms in pseudoanonymised format at the treatment site (Table 1). Furthermore, patients will be requested to complete the CAT and mMRC Dyspnoea Scale. Follow-up visits will be conducted one and three months after discharge. If the patient does not attend the visit, the patient will be contacted for a new follow-up or - if not able to meet for an appointment at the hospital - a home visit by a doctor assigned to the project. At the one month and the three month follow up visits the following data will be assessed: BMI, HbA1c (only at the one month follow-up), spirometry values, CAT score, mMRC, CTX, P1NP, PTH (only at the three month follow-up), D-vitamin status (only at the three month follow-up), cumulative systemic corticosteroid dose, the period between index AECOPD and the next AECOPD, COPD related re-admission rate, dyspepsia or ulcer complications (gastrointestinal bleeding) and new infections treated with antibiotics since study entry.

**Table 1 Tab1:** Data collected at baseline and follow-up visits

Data collected	Study period		
	Baseline	1-month	3-month
Demographics	X		
Daily blood glucose measurements	X		
Daily leukocyte differential count^a^	X		
Arterial blood gases and Chest X-ray	X		
Testing for diabetes (HbA1c)	X	X	
Spirometry	X (day 1 + day 3)	X	X
Height measurement & vital signs	X		
Weight measurement	X	X	X
Vitamin D and PTH levels	X		X
COPD Assessment Test (CAT)	X	X	X
Medical Research Council Dyspnoea Scale	X	X	X
Bone Turnover Markers (CTX, P1NP)	X	X	X
Questionnaire on general health condition		X	X
Pregnancy test	X		

^a^Completed by patients in the intervention group only

Collection of data and storage will comply with Good Clinical Practice guidelines as defined by the International Conference on Harmonisation guidelines [18]. Analysis of anonymised data will be conducted by the principal investigator with assistance from site investigators and supervisors.

